### Interventions

Participants who are newly enrolled in the standardized community-based rehabilitation will be designated to join the social worker organizations where the residence of the drug users are registered and have to sign a contract with their corresponding social workers. Participants need to visit their corresponding social workers and receive illicit drug test every 2 months. Social workers will help their corresponding clients to apply for social benefits accordingly and provide counseling irregularly if necessary.

The integrated rehabilitation group will receive the standardized community-based rehabilitation described above and simultaneously receive a 6 months integrated rehabilitation based on CAREs. CAREs was developed by the department of addiction research in Shanghai Mental Health Center (SMHC), with functions including education, support, psychological intervention and other functions.

The main structure of the system consists of three parts: (a) an APP for users; (b) a web page for service providers such as social workers; (c) server to store data and information (see Figure 1).

**Figure 1 F1:**
[figure not shown]
Frame diagram of Community-based Addiction Rehabilitation Electronic System (CAREs): **(A)** Users manage to get immediate support and intervention through CAREs installed in smart phone devices; **(B)** Users' corresponding social workers can know their clients' current situation by using the web page; **(C)** All data will be stored in a secure server and double backuped, only doctors and executives are eligible for access.

The app provides disease and health knowledge, education, screening, assessment and monitoring, craving and emergency coping skills, and patient self-management to improve recovery outcomes among drug users in communities (see Table 1 and Figure 2).

**Table 1 T1:** Corresponding function of each component of the mobile terminal of the community-based addiction rehabilitation electronic system(CAREs).

**Component**	**Function**
Setting and personal information	If the users use the addiction substance except cigarette and alcohol, then they need to add real name, user name (voice-print password), the main use of drugs, community drug addiction/rehabilitation information
Regular reminders	People who are enrolled in the community drug addiction/rehabilitation will be reminded to do the urine test (Community addiction: the first year once a month, the second year once every 2 months, the third year once every 3 months; community rehabilitation: the first year once every 2 months) Drug abusers has left the community addiction/rehabilitation, etc
Survey (every week)	Periodically evaluated and presented curves. Assessment information include: drug use in the past week, craving (visual simulation, VAS), depression (PHQ-9), anxiety (GAD-7), nicotine dependence scale (FTND)
Popular science pushing	According to types of the material and ASSIST score which was checked by users, the content of science popularization of drug rehabilitation and propaganda was pushed
Immediate response to craving	Craving assessment (using visual simulation, VAS), the coping methods for craving, include guided language, relaxation training (music, video, etc.)
Rehabilitation process management	Combine the information collected by Survey, pushing intervention based on time
Coping with stress events	Stress/Trigger assessment (time, location, nature of events), targeted push intervention
Board	According to Survey, the network is made up of the users and the top of information was showed
Support and outreach	Transfer of external resources, providing professional manual service hotline. For example, the 24 h hotline for the addiction department of Shanghai mental health center and the 24 h hotline for social workers
Emergency response	Push the first aid common sense, locate the nearby emergency hospital, and so on for emergency use
Medical condition	urinary drug testing (different types), syphilis qualitative, hepatitis C qualitative, HIV qualitative screening, urinary routine, liver function(ALT, AST),renal function (urea nitrogen, creatinine), electrocardiogram, B-ultrasonography, thoracic ultrasonography (X-ray).

**Figure 2 F2:**
[figure not shown]
“Screenshots” taken on a phone device illustrating the user interface: no Regular reminders and Rehabilitation Process Management above for: (1) Regular reminders will only be used when users receive messages from service providers or server; (2) Rehabilitation process involves in some privacy of the patients. For better understanding, we translated some Chinese on the pages into English. CAREs actually is presented in Chinese.

The corresponding social workers can be linked with their clients via CAREs webpage. By using the webpage, social workers could review their corresponding clients' survey (self-report craving, stress events, medical laboratory testing results, and location information) and could give a response or arrange a face-to-face meeting accordingly. Social workers will also receive reminds and messages automatically, so that they could know who misses urine test, or the time who reports high craving or stress events (see Table 2 and Figure 3).

**Table 2 T2:** Corresponding function of each component of the service provider terminal of the community-based addiction rehabilitation electronic system(CAREs).

**Component**	**Function**
Login/register	Service information
Group management	To achieve docking and management between the service and mobile terminal users
Information summary	Information include: The number of times users use the mobile terminal, rehabilitation process information (in time for the horizontal axis), Survey information (craving, stress events, medical laboratory testing), location information
Reminder	According to the situation of each mobile terminal user, push urine test reminder, treatment reminder, high-risk situation reminder (mobile terminal users report high desire or stress events)
Interaction	Push information (implemented on the “support and outreach” section of the mobile terminal).

**Figure 3 F3:**
[figure not shown]
The main “screen” of the service provider web portal. For better understanding, we translated some Chinese on the page into English. The webpage is actually presented in Chinese.

Data including account information, statistics of user end, mobile user location information, and interaction between mobile users and social workers will be stored on a secure server. Registering to use CAREs is free and participants will receive an extra 50 RMB as compensation of potential cost on mobile data during the study period. At the end of the study, participants in integrated rehabilitation group could have the chance to gain the smartphone as a motivation to comply with the research protocol.

### Outcomes

The primary outcome is the performance on urine drug screen (UDS) which will be carried out regularly during the study period twice per week. The results of urine tests will be examined in the difference of proportion of drug-positive samples between two groups. Urine test kit will be used to test drug use including heroin, amphetamine-type stimulants, marijuana, cocaine, and ketamine. A subject who does not submit urine samples during the intervention period or who refuses to submit a sample even if he/she is present at the site will be considered as having a positive UDS.

Secondary outcomes include: (a) longest duration of sustained abstinence, defined as the longest continuous record weeks of negative urine drug screen samples; (b) interaction with social workers in the addiction recovery services: the days that participants interact with their corresponding social workers will be collected during the study period. Any phone call, SMS, face-to-face meeting, or communication via CAREs will be considered as one interaction; (c) the decrease rate of addiction-related issues severity index: the Chinese translation of the Addiction Severity Index (ASI) that has good reliability and validity in China will be used to assess the severity of addiction at enrollment and 6 months after enrollment. The reliability and validity of the Chinese version of the instrument have been assessed (21, 22). The internal consistency of the seven dimensions was judged to be acceptable (alpha = 0.44~0.79), the test-retest reliability was good (ICC = 0.68~0.84), and the inter-rater reliability was good (ICC = 0.87~0.98). The descent rate will be counted via dividing the minus value between baseline score and 6 months score by baseline score (assessments completed at assessment phases shown in Table 3).

**Table 3 T3:** Assessments completed at assessment phases.

**Assessments**		**Assessment Phase**		
		**T1**	**T2**	**T3**

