### Discontinuation

The end of the study is defined as participants finishing the evaluation at the end of 6 months, or withdrawal from the study. Subjects are free to withdraw from the study at any time for any reason. They could also be withdrawn by the investigator, if necessary, to protect their health and the safety or integrity of the study data. The principal investigator could withdraw a participant from the study for any of the following reasons: (a) rehabilitation failure (having incarceration or readmission to compulsory treatment or both; (b) a protocol deviation that might compromise data integrity, protocol compliance or subject safety; (c) a participant's request to be discontinued from the study (i.e., a subject declines further study participation).

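### Unsubmitted urine samples are scored as drug-positive, while the described prompts and the compliance incentive exist only in the CAREs arm, so a difference in attendance can pass for a difference in drug use

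*Protocol article*

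**What the plan says.** **Outcome and scoring rule (Outcomes).** Urine screening is "carried out regularly during the study period twice per week", and "The results of urine tests will be examined in the difference of proportion of drug-positive samples between two groups". Failure to hand in a sample while the intervention is running counts as positive, and so does refusal: anyone that "refuses to submit a sample even if he/she is present at the site will be considered as having a positive UDS". The rule is the same in both arms.

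**What only the CAREs arm is described as having (Interventions).**
- Table 1, regular reminders: app users "will be reminded to do the urine test". The intervals listed there are the routine ones; for community rehabilitation in the first year this is one test every two months. Table 2 adds a urine-test reminder sent from the provider side, with no schedule.
- Provider webpage: social workers get automatic messages "so that they could know who misses urine test".
- Compensation: "participants in integrated rehabilitation group could have the chance to gain the smartphone as a motivation to comply with the research protocol". The section on post-trial care calls the phone a gift.

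**Control arm (Trial design, Interventions).** Controls get routine rehabilitation alone, in which they "receive illicit drug test every 2 months". No matching prompt, alert or incentive is described for them.

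**Withdrawal (Discontinuation).** The investigator may withdraw a participant, among other reasons, for "a protocol deviation that might compromise data integrity, protocol compliance or subject safety". The end of the study includes withdrawal. The section does not say how samples due after withdrawal are scored.

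**The concern.** Under this rule the primary outcome has two components: drug use in the samples handed in, and failure to hand samples in. Counting a missed sample as positive is a familiar convention in addiction trials, and it does little harm to the comparison when both arms miss samples at similar rates. Here the plan combines it with features that could raise submission and are described for one arm only. One of them, the smartphone, is by the protocol's own account meant to encourage compliance.

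The primary aim is abstinence. If CAREs participants attended more often but used drugs just as much, the scored result would still show fewer positives in their arm, and the trial could not tell the two explanations apart from the scored outcome alone. The first secondary outcome, the longest run of negative samples, is exposed in the same way if a missed sample breaks the run.

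**Working it through.** **Inputs**
- Planned samples per participant: 2 per week × 26 weeks = 52 (Outcomes).
- Routine tests in six months at one every two months: 6 / 2 = 3 (Interventions; Table 1).
- True positive rate p: assumed 0.40, equal in both arms. This borrows the 40% in the Sample size section, read as the control rate of drug use; the wording there is not explicit.
- Miss rates by arm: not given. The only related figure is an overall 20% loss to follow-up (Sample size). All values below are assumptions.

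**The plan's own effect.** A 60% reduction from 40% gives 0.40 × (1 − 0.60) = 0.16, so the planned difference is 0.40 − 0.16 = 0.24, or 24 points. The stated sample size is not needed for this point.

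**Formula.** With a share m of samples missed and scored positive, scored positivity = m + (1 − m)p. With the same p in both arms, the difference produced by the rule alone is

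(m_control − m_CAREs)(1 − p).

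This takes missed samples to be truly positive as often as the others. If they are positive more often, the factor (1 − p) shrinks. If every missed sample were truly positive, the rule would be correct and the artefact zero.

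**Results at p = 0.40, no effect on drug use**

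| Missed, control vs CAREs | Scored positive, control | Scored positive, CAREs | Artefact |
|---|---|---|---|
| 20% vs 20% | 0.20 + 0.80 × 0.40 = 0.52 | 0.52 | 0 points |
| 20% vs 15% | 0.52 | 0.15 + 0.85 × 0.40 = 0.49 | 3 points |
| 20% vs 10% | 0.52 | 0.10 + 0.90 × 0.40 = 0.46 | 6 points |
| 30% vs 10% | 0.30 + 0.70 × 0.40 = 0.58 | 0.46 | 12 points |

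A lower p enlarges the artefact. At p = 0.20, 20% versus 10% missed gives (0.20 − 0.10) × 0.80 = 8 points.

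**Scale.** At p = 0.40, reproducing all 24 planned points by attendance alone would need a gap in miss rates of 0.24 / 0.60 = 40 percentage points.

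**If reminders reach only the routine tests.** Suppose the 3 routine tests count among the 52 samples, and reminders raise attendance at those 3 by an assumed 30 points. The contribution is (3 / 52) × 0.30 × 0.60 = 0.010, about 1 point. The alerts and the smartphone are not in this figure, because the text does not limit them to the routine tests.

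**The case against.** The case on the other side has several parts, and much of it stands.

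- **Reach of the reminders.** The only schedule given is the routine one, so the protocol does not show that clients are prompted for the twice-weekly samples. This stands and limits the size. It does not remove the point: the provider-side reminder and the missed-test alert carry no schedule, and the smartphone is tied to the research protocol, of which study sampling is a part.
- **Alerts.** Data collection has each participant's own social worker collect the urine data in both arms, so control-arm workers may also know who missed a test. What CAREs adds is automation.
- **Smartphone.** It is a possibility at study end, not a promised reward, and complying could mean using the app. It is nevertheless offered to one arm only.
- **Direction.** A reader might infer that the bias must always favour CAREs. The documents do not support that. The rule favours whichever arm submits more samples, and CAREs also brings weekly surveys and location information visible to social workers, which could lower participation.
- **Withdrawal.** A reader might infer that investigator withdrawal contradicts the intention-to-treat principle stated under Data management. It need not: the scoring rule can be read as counting samples missed after withdrawal as positive, which keeps those participants in. What remains is that Discontinuation does not say so.
- **Analysis plan.** Sensitivity analyses may be in a document not shown. Their absence here is not held against the plan. The scoring rule and the one-sided incentive are fixed in this document, and no later analysis can make the incentive equal.

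**Conclusion.** The point holds in a conditional form. As written, the plan can turn a difference in sample submission into an apparent difference in abstinence, because the scoring rule makes attendance part of the outcome and the described prompts and incentive belong to one arm. If submission is higher under CAREs, the bias is towards CAREs.

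The size cannot be determined from the protocol. At p = 0.40 the illustrations run from 3 to 12 points against a planned 24, and the contribution of reminders limited to routine tests would be about 1 point. These figures assume the miss rates, equal true drug use in both arms, and missed samples that are positive as often as the others.

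Two stronger conclusions are tempting and should not be drawn. One is a specific, large false-positive rate: it would depend on arm-specific miss rates and between-participant variation that the protocol does not give. The other is that the trial cannot answer its primary question. It can, provided that submission turns out similar in the two arms, or that the result does not depend on how missed samples are scored.

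**What to change.** 1. **Equalise what drives submission of study samples.** State which tests the reminders, alerts and smartphone offer cover. For study urine samples, use the same prompts in both arms, sent automatically or by study staff. State that these prompts do not count as social-worker interactions, since the second secondary outcome counts any SMS or call as contact. Offer the smartphone on the same terms in both arms, or detach it from protocol compliance.
2. **Support the scoring rule.** It can stay as the primary rule. Report the share of planned samples submitted by arm, and set beside it an analysis of submitted samples with multiple imputation and a tipping-point analysis. Claim an effect on abstinence only if the direction holds without scoring missed samples as positive.
3. **Settle follow-up after withdrawal.** State that participants withdrawn from the intervention remain in outcome follow-up where consent allows, and that everyone is scored against the full planned set of samples.

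The cost is automated messages to controls, sharing the phones across arms or changing the terms of the offer, and a few added analyses. The downside is that controls receive slightly more contact than in routine care.

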### Data management

Intention-to-treat principle will be used in the statistical analysis. All statistical analyses will be conducted using SPSS Statistics (version 22) (24). Chi-square tests and ANOVAs will be used to compare characteristics of the members of the two groups. Primary outcome and secondary outcomes (results of urine illicit drug tests between the groups, the days that participants interact with their corresponding social workers) will be compared between groups using analysis of ANOVAs. Considering behavioral clinical trials often find data missing at the end of trials due to incomplete evaluations, Generalized Estimating Equations (GEE) will be used to compare the seven dimensions scores of the ASI between group across the study period. Any unfavorable changes to participants during the study period will be recorded. Since this study does not impact participants' routine care and is examining the effect of an integrated community-based rehabilitation for drug abusers in communities, no serious adverse events are anticipated and no interim analyses are planned.

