### Ancillary and post-trial care

At the end of the study, participants from integrated rehabilitation group have the chance to gain the smart-phone installed with the study APP as a gift accordingly. All participants will be maintained in community-based rehabilitation after this study.

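### Interaction days are compared as raw totals over a study period that can end at withdrawal, so unequal retention alone can separate the arms

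*Protocol article*

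**What the plan says.** Three sections of the protocol article fix this outcome.

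- **Outcomes**, secondary outcome (b): "the days that participants interact with their corresponding social workers will be collected during the study period". The quantity is a number of days, with no denominator.
- **Discontinuation**: "The end of the study is defined as participants finishing the evaluation at the end of 6 months, or withdrawal from the study". One listed reason for withdrawal by the investigator is "rehabilitation failure (having incarceration or readmission to compulsory treatment or both"; others are a protocol deviation and the participant's own request.
- **Data management**: "the days that participants interact with their corresponding social workers) will be compared between groups using analysis of ANOVAs". No rate, offset or adjustment for time observed is named.

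Incomplete follow-up is dealt with for other outcomes. Outcomes counts an unsubmitted urine sample as positive. For the ASI, Data management says that "Generalized Estimating Equations (GEE) will be used to compare the seven dimensions scores of the ASI between group across the study period", and gives missing data as the reason. Nothing comparable is said for interaction days beyond the general statement that "Intention-to-treat principle will be used in the statistical analysis".

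**The concern.** A total of days depends on two things: how often a participant has contact and how long that participant is observed. If counting stops when someone leaves, a person who withdraws in week 8 contributes an 8-week count, and the ANOVA treats it like a 26-week count.

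This biases the comparison only if time observed differs between arms, and the article gives a reason to expect that it may. According to Interventions and to Ancillary and post-trial care, only integrated-arm participants may receive the smartphone. It is offered at the end of the study and is meant to encourage compliance. In addition, if CAREs supports abstinence as hypothesised, fewer CAREs participants may be withdrawn for rehabilitation failure.

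Interaction between users and providers is the first part of the secondary aim. With unequal retention, the planned analysis could report a difference in interaction that reflects only who stayed, or could hide a real difference in contact. The problem does not depend on whether messages through CAREs count as contact: it remains if only calls and face-to-face meetings are counted.

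**Working it through.** The article states no expected value for outcome (b), so there is no figure of its own to reproduce. The check asks how far raw totals separate when the true contact rate is the same in both arms.

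**Inputs from the article**
- Loss to follow-up: 20% overall, no figure by arm (Sample size).
- 35 participants per arm (Sample size, Allocation).
- 6 months of follow-up (Participant timeline), taken as 26 weeks.

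**Assumptions**
- The same contact rate of r days per week in both arms.
- Counting stops at withdrawal, and those who leave do so halfway through on average.
- Loss by arm (d_ctl for control, d_int for CAREs) averages 20%.

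**Formula**

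Expected total = 26r × [(1 − d) + 0.5d] = 26r × (1 − d/2)

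Ratio, CAREs to control = (1 − d_int/2) / (1 − d_ctl/2)

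The contact rate cancels from the ratio.

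| Loss, control / CAREs | Ratio | Totals at 1 day/week, control vs CAREs | Totals at 2 days/week, control vs CAREs |
|---|---|---|---|
| 20% / 20% | 0.90/0.90 = 1.00 | 23.4 vs 23.4 | 46.8 vs 46.8 |
| 25% / 15% | 0.925/0.875 = 1.06 | 22.75 vs 24.05 (gap 1.3) | 45.5 vs 48.1 (gap 2.6) |
| 30% / 10% | 0.95/0.85 = 1.12 | 22.1 vs 24.7 (gap 2.6) | 44.2 vs 49.4 (gap 5.2) |

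The gap in days, unlike the ratio, depends on the assumed contact rate. If contact were only the routine visit every 2 months, about 3 in 6 months, the 30%/10% split would give 3 × 0.85 = 2.55 against 3 × 0.95 = 2.85, a gap of 0.3 days.

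**Effect on the test.** In a simulation of 20,000 trials with 35 per arm, withdrawal times were uniform over 26 weeks and the true rate was 1 day per week in both arms. The share of ANOVAs significant at 5% was:
- about 5% with equal loss;
- 7% to 11% at 25%/15%;
- 12% to 28% at 30%/10%.

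The lower figure in each range allows contact rates to vary between people (gamma-Poisson, shape 4); the upper is pure Poisson. Expressed as days per observed week, the same data gave 1.00 in both arms in each of these scenarios.

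**The case against.** The strongest objection is that the article never says outright that counting stops at withdrawal. That follows from joining the wording of outcome (b) to the definition of the end of the study. Participant timeline sets a 6-month period with assessment at 6 months after randomisation, Table 3 places interaction at the completion of the intervention, and the analysis is by intention to treat. These allow a fixed 6-month window, under which nothing is truncated and there is no bias. The objection stands as a limit on certainty. It does not remove the point, because no collection after withdrawal is described for this outcome and the only participant-level end given includes withdrawal.

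A reader might go further and infer that mandatory contact continues for everyone who leaves, so that real contacts go unrecorded in every case. The article does not support that:

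- "All participants will be maintained in community-based rehabilitation after this study" concerns care after the study, not after early withdrawal.
- Routine contact is sparse: "Participants need to visit their corresponding social workers and receive illicit drug test every 2 months".
- After incarceration or compulsory treatment, community contact really stops, and a low total is then a true result.
- Urine screening is twice weekly, and Data collection has the participant's social worker collect those results. If such visits count as contact, they may end with study participation.
- No breakdown of withdrawal reasons is given.

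A reader might also take 5.2 days as the size of the bias. It is not a finding about this trial: the contact rate, the timing of withdrawal and the split by arm are all assumed. The direction is not documented either; if CAREs retained fewer people, the bias would reverse.

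It is also fair to say that total interaction over 6 months is a legitimate intention-to-treat target. Replacing it with a rate for all withdrawals would change the question, so a rate should not be the main remedy. Finally, the handling of partial follow-up is often left to a statistical analysis plan. Here, however, the article itself fixes the outcome, the end of observation and the test, and together they produce the problem.

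**Conclusion.** The point holds conditionally. As written, the outcome, the definition of study end and the ANOVA combine to compare totals observed over different lengths of time. At an equal contact rate, the better-retained arm scores higher by the ratio (1 − d_int/2)/(1 − d_ctl/2): nothing at equal loss, about 6% at 25%/15% and about 12% at 30%/10%.

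This rests on three assumptions: that counting stops at withdrawal, that withdrawal falls at mid-study on average, and that loss differs by arm. The one-arm incentive makes the last plausible, but the article gives no size for it.

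This is one secondary outcome in a study described as a pilot. It is worth correcting because it bears on a named aim and the correction is cheap. It is not an established error of known size.

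**What to change.** 1. **Fix the window.** Define outcome (b) as the number of days with contact over 6 months from randomisation, for every randomised participant. After withdrawal from other study procedures, continue to take contact days from the social worker's records where consent allows.
2. **State how confinement is counted.** Keep time in incarceration or compulsory treatment in the window, as days without community contact.
3. **Fallback.** Where records after withdrawal cannot be obtained, analyse days with a count model (negative binomial, or Poisson with robust errors) with log observed time as offset, instead of ANOVA on truncated totals. Report raw totals descriptively.

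The cost is slightly more record collection, consent wording that covers it, and a few sentences in Outcomes and Data management. The fallback assumes that contact before withdrawal represents contact after it. That is doubtful if study urine visits make up much of the contact, which is why the fixed window comes first.

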## Methods and analysis

### Trial design

This is a randomized controlled trial (RCT). The study uses parallel group design and is a superiority trial to explore whether the integrated rehabilitation based on CAREs promotes drug abusers to stay abstinent. The study divides participants into integrated and standardized community-based rehabilitation groups in a ratio of 1:1 and has 2 arms: the participants in integrated rehabilitation group will receive regular community-based rehabilitation plus CAREs with their matched social workers, the participants randomized to the standardized community-based rehabilitation group will only receive routine community-based rehabilitation.

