### Data collection

The majority of study-specific data outlined in the protocol will be entered onto the paper Case Report Form (CRF) by site coordinators in accordance with the Clinical Completion Guidelines. Urine test data will be collected by each participant's corresponding social worker. These paper gees will be collected at each monitoring visit and double data will be entered by specialists. The CAREs usage data among integrated rehabilitation group will be collected automatically from the system, whereas those electronically data will be maintained on a secure server at SMHC and will be downloaded periodically for storage in a password-protected data file accessible by two study personnel.

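### Days of interaction with social workers include an app channel open only to the integrated arm, which tilts the between-arm comparison upward and can hide replaced calls or visits

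*Protocol article*

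**What the plan says.** The Outcomes section of the Protocol article defines secondary outcome (b) in days: "the days that participants interact with their corresponding social workers will be collected during the study period". It then lists what qualifies: "Any phone call, SMS, face-to-face meeting, or communication via CAREs will be considered as one interaction".

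The Trial design section sets out who has the app. On one side, "participants in integrated rehabilitation group will receive regular community-based rehabilitation plus CAREs with their matched social workers"; on the other, "the participants randomized to the standardized community-based rehabilitation group will only receive routine community-based rehabilitation".

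Table 2 (Interventions) describes the provider terminal. Its interaction component consists of pushing information to the client's app. A separate reminder component can "push urine test reminder, treatment reminder, high-risk situation reminder".

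On data capture, Interventions says that "interaction between mobile users and social workers will be stored on a secure server". Data collection adds: "The CAREs usage data among integrated rehabilitation group will be collected automatically from the system". For other data it says only that "The majority of study-specific data outlined in the protocol will be entered onto the paper Case Report Form (CRF) by site coordinators".

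Data management compares the days of interaction between arms by ANOVA. The Discussion expects more interaction in the intervention group. The Introduction gives the aim that this serves: the impact of CAREs on interaction between users and providers.

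**The concern.** Four channels score on this outcome, and controls have three of them. Any day on which the only contact is through CAREs raises the total in one arm and cannot occur in the other. The definition does not say that a CAREs communication must be an exchange between two people. Since the table describes the provider's interaction function as pushing information, a one-way message could be scored.

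What is at stake is how the secondary aim is read. A significant ANOVA could arise with calls, SMS and meetings unchanged, and it would then partly restate that one arm received the app. The pooled measure also works in the opposite direction: if app messages took the place of visits or calls, the total could stay level and the shift would go unseen.

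**Working it through.** The article states no figure for this outcome, so there is nothing to reproduce. The check asks how far the definition alone can move the ANOVA when contact outside the app is the same in both arms.

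**Inputs from the article**
- Period: 6 months, taken as 26 weeks, D = 26 × 7 = 182 days.
- Participants per arm: 35 (Sample size); after the stated 20% loss, 35 × 0.8 = 28.
- Routine contact, low end: a visit every 2 months (Interventions), 6 / 2 = 3 days, plus irregular counselling.
- Routine contact, high end: urine tests twice per week (Outcomes), 26 × 2 = 52 days, if a test counts as contact. The article does not settle this. Data collection has the social worker collect the urine data, while Blinding says that the testers differ from those who give the intervention.

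**Assumptions not in the article**
- Mean days with a call, SMS or meeting (O): 3 to 52, equal in both arms.
- Mean CAREs contact days (C), integrated arm only: 6, and 26 (weekly) as a heavier case.
- Contact rates vary between persons with a coefficient of variation of about 0.7 (gamma).
- CAREs days fall independently of other contact days.

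**Expected excess in days.** A CAREs day adds to the total only if there was no other contact that day, so the excess is about C × (1 − O / D).
- C = 6, O = 3: 6 × (1 − 3/182) = 5.9 days.
- C = 6, O = 52: 6 × (1 − 52/182) = 4.3 days.

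The simulation gave 5.9 and 4.4.

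**How often the ANOVA significantly favours the intervention** (alpha 0.05, 1,500 simulated trials per cell)

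| Mean other contact days | 6 CAREs days, n = 35 | 6 CAREs days, n = 28 | 26 CAREs days, n = 35 |
|---|---|---|---|
| 3 | 100% | 100% | 100% |
| 6 | 99% | 96% | 100% |
| 12 | 70% | 59% | 100% |
| 26 | 21% | 16% | 99% |
| 52 | 8% | 7% | 57% |

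The rate that should favour the intervention by chance is 2.5%. The excess in days changes little down the first column. The rate falls because the assumed spread between persons grows with the mean and swamps the excess.

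**Shared channels only.** With CAREs days left out, rejection in either direction returned to 4.3% to 5.5%.

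**Full replacement.** If each CAREs day displaces another contact day (C = 6, n = 35), rejection was 7.0% at O = 12 and 4.5% at O = 26. The total then hardly moves although the mix of contact has changed.

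**The case against.** The strongest defence is that CAREs is meant to create contact. The aim is its impact on interaction, so contact through CAREs is part of the effect, and leaving it out would make contact moved to the app look like a loss. This stands: the all-channel total is a legitimate measure and should stay. It does not make that total sufficient, because alone it cannot separate more contact from the supply of a new channel.

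Stronger readings are tempting, and the article does not support them:
- **The integrated arm must score higher.** The unit is days, so a CAREs message on a day with another contact adds nothing, and replacement can remove the excess.
- **Any use of the app meets the aim.** The outcome requires interaction with the social worker. Completing surveys or using relaxation material is not that.
- **Weekly CAREs contact means 26 days against 3.** The weekly rate is an assumption. The comparison sets an increment against a total, and it leaves out calls, SMS, counselling and the twice-weekly tests.
- **The unit is inconsistent.** The Abstract, Outcomes and Data management all name days. The sentence on what counts as one interaction is loose, but it can be read as listing the contacts that qualify.
- **Automatic reminders are scored.** Table 2 lists reminders apart from interaction. The ambiguity about one-way messages comes from the interaction row.
- **Calls and meetings are logged on paper while app contact is automatic.** The article says only that most data go on paper forms and does not say how these contacts are logged. Unequal capture is possible but not shown.

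This is also one secondary outcome in a study that calls itself a pilot, and the urine-test primary outcome is untouched.

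**Conclusion.** The concern holds as a built-in upward tilt in the integrated arm, not a guaranteed difference. It rests on three statements in the article: CAREs communication counts, only one arm has CAREs, and the arms are compared on the resulting days. A difference on this measure could partly restate that the app was supplied, and a null result could conceal replacement of calls or visits.

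The size cannot be fixed from the article. With 6 CAREs days on average and 35 per arm, the rate of a significant result favouring the intervention, with no change outside the app, runs from about 100% at 3 routine contact days to about 8% at 52. These rates rest on the assumed contact frequencies, the assumed spread and independent timing. The direction of the tilt does not depend on the routine contact level, but it does depend on CAREs days not fully replacing other contact. The point deserves correction and does not threaten the primary result.

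**What to change.** Keep days as the unit throughout, and make these changes to secondary outcome (b):
- Count a day only if it has at least one person-to-person exchange with the participant's social worker. State that automatic pushes and reminders do not count.
- Record the channel of each contact, in the same way in both arms. The full protocol or its forms may already do so.
- Compare arms on days with contact through channels open to both (call, SMS, face-to-face), alongside the all-channel total.
- Report CAREs communication separately, as uptake in the integrated arm.
- State that an all-channel difference alone will not be taken as evidence of better contact.
- State whether attending a study urine test counts as contact, and reconcile the 2-monthly and twice-weekly test schedules for this purpose.

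The cost is a revised outcome definition, one field on the contact record and one further comparison. The drawback is that contact moved to the app lowers the shared-channel figure, so neither result should be read without the other.
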